### Cost benefit analysis

There are a number of techniques available with which to elicit a monetary value of the benefit of health care. Discrete choice experiments (DCE), more formally known as conjoint analysis, are a commonly employed approach to eliciting stated preferences [50]. When DCEs include cost information, it is possible to manipulate the results to given information on respondents' willingness-to-pay (WTP) for a service, such that a CBA can be undertaken.

A literature review will be conducted to determine health and non-health preferences (attributes) for service provision, this together with semi-structured interviews and focus group discussions with patients, parents and health professionals, will inform the development of the attributes and levels for the DCEs [51-53]. Once the attributes have been identified, and the levels and costs set by the project team, an orthogonal design will be created. Both the control and the treatment arm groups will complete the DCE questionnaire (parents in children under 16 years of age) at baseline. This will provide information from which to indirectly establish willingness-to-pay, and undertake a CBA. As an added dimension it is proposed that patients/parents will undergo the same experiment at the completion of the trial. This will allow an evaluation of whether exposure to the intervention (as for those in the intervention arm) changes their preferences for the intervention.

### Sample size

The sample size for the study has been pre-determined by power analysis of the primary outcome measure; the impairment domain of the JAFI questionnaire (JAFI-IMP. Sixty patients (30 in each trial arm) will allow detection of a 1 point reduction in the JAFI-IMP score (a conservative assumption determined by the trial steering committee) at six months from baseline at a significance level of p < 0.05 and power of 90%. These figures take into account the estimated potential participant drop out rate over the first six months of the trial (8 patients in each trial arm). The exploratory nature of the trial will permit in-depth examination of the suitability of the JAFI as a primary outcome measure for use in definitive multi-centre trials.

### Statistical analysis

The primary analysis will compare the JAFI scores for each dimension between the intervention and control group at six months from baseline. This is to be conducted using a two-sided t-test. Should the distribution of change scores be skewed, a Mann Whitney test may be used to analyse the primary outcome variable in preference to a t-test. The longitudinal JAFI scores, at 0, 6, and 12 months will be analysed using repeated measures ANOVA with post hoc testing to identify significant differences between treatment groups and time points.

Core outcome variables scores for each group will be compared using a confidence interval for the difference in proportions. This will be based on a normal approximation to the binomial distribution.

Changes in predetermined gait variables (see Patients assessments and outcome measures section) from baseline to 12 months from baseline will be investigated within each treatment group using a one-sample procedure (t test or Signed Ranks test) and compared across treatment groups using the equivalent two-sided procedure (t test or Mann-Whitney test).

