**Methods/design:**

An exploratory phase II non-pharmacological randomised controlled trial where patients including young children, adolescents and adults with juvenile idiopathic arthritis and associated foot/ankle problems will be randomised to receive integrated podiatric care via a new foot care programme, or to receive standard podiatry care. Sixty patients (30 in each arm) including children, adolescents and adults diagnosed with juvenile idiopathic arthritis who satisfy the inclusion and exclusion criteria will be recruited from 2 outpatient centres of paediatric and adult rheumatology respectively. Participants will be randomised by process of minimisation using the Minim software package. The primary outcome measure is the foot related impairment measured by the Juvenile Arthritis Disability Index questionnaire's impairment domain at 6 and 12 months, with secondary outcomes including disease activity score, foot deformity score, active/limited foot joint counts, spatio-temporal and plantar-pressure gait parameters, health related quality of life and semi-quantitative ultrasonography score for inflammatory foot lesions. The new foot care programme will comprise rapid assessment and investigation, targeted treatment, with detailed outcome assessment and follow-up at minimum intervals of 3 months. Data will be collected at baseline, 6 months and 12 months from baseline. Intention to treat data analysis will be conducted.

A full health economic evaluation will be conducted alongside the trial and will evaluate the cost effectiveness of the intervention. This will consider the cost per improvement in Juvenile Arthritis Disability Index, and cost per quality adjusted life year gained. In addition, a discrete choice experiment will elicit willingness to pay values and a cost benefit analysis will also be undertaken.

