### Initial assessments and outcome measures

At baseline all participants will be assessed to ensure they satisfy the inclusion criteria. Demographic and disease characteristic data such as age, gender, height, weight, disease sub-type, date of diagnosis, disease duration will also be recorded. All baseline assessments, primary and secondary outcome measures will be recorded prior to allocation to either the usual care arm or the intervention arm. The medical and physiotherapy care plans will be committed to paper prior to randomisation.

The primary outcome is the Juvenile Arthritis Foot Disability Index (JAFI) [31]. This questionnaire is organised by three dimensions related to impairment (9 items), activity limitation (14 items) and participation restriction (4 items) with a 5-point Likert scale for each item. Each point on the 5-point likert scale represents the frequency of the foot problem stated for that particular item during the past week (0 = Never, 1 = Occasionally/Less than once a week, 2 = Sometimes/Once a week, 3 = Frequently/Two to three times a week, and 4 = Always). Median scores are computed for each dimension. The JAFI is completed by parents of children <10 years and self-completed by adolescent children = 10 years of age. It has been shown to be to be valid and reliable for assessing foot-related impairment and disability among children/adolescents with JIA [31]. The JAFI has not yet been formally validated for use in adult patients with JIA. This questionnaire will be administered at baseline, then 6 (by post) and 12 months from baseline. The exploratory nature of the trial will permit in-depth examination of the suitability of the JAFI as a primary outcome measure for use in definitive multi-centre trials.

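### The primary analysis compares all three JAFI dimensions at six months, but only the impairment domain at six months is powered and the abstract adds 12 months; no rule says which comparison decides

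*Protocol article*

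**What the plan says.** Four places in the protocol article bear on the primary outcome.

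- **Abstract, Methods/design:** the primary is the foot-related impairment score, taken from the questionnaire's "impairment domain at 6 and 12 months".
- **Initial assessments and outcome measures:** "The primary outcome is the Juvenile Arthritis Foot Disability Index (JAFI"), with no dimension singled out. The same section says: "This questionnaire is organised by three dimensions related to impairment (9 items), activity limitation (14 items) and participation restriction (4 items"), and "Median scores are computed for each dimension". No total score is described. The sections on blinding and on follow-up also call the JAFI as a whole the primary outcome.
- **Sample size:** the number of patients comes from a "power analysis of the primary outcome measure; the impairment domain of the JAFI questionnaire". It is set for a 1-point difference in JAFI-IMP at six months, p < 0.05 and 90% power, with 8 drop-outs per arm allowed for over the first six months.
- **Statistical analysis:** "The primary analysis will compare the JAFI scores for each dimension between the intervention and control group at six months from baseline", by two-sided t-test. The section then refers to one primary outcome variable, in the singular, without naming it. JAFI scores at 0, 6 and 12 months go into a separate repeated measures ANOVA with post hoc tests.

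**The concern.** The section that governs the analysis makes the primary comparison plural, while the section that justifies the trial's size makes it singular. Because no total score is defined, the three dimensions cannot be read as one endpoint. The abstract adds a second time point for impairment.

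No hierarchy, split of the significance level or combining rule is given, and the text does not say which comparison settles the question. A nominally significant result on activity limitation or participation restriction could therefore be reported as the primary finding under the literal wording, although neither was used to size the trial. An unseen analysis plan could add error control, but it would still have to choose between statements that this article makes and that do not agree.

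**Working it through.** **1. The plan's own figure.** Inputs from the Sample size section: difference 1 point, level 0.05, power 90%, 30 per arm, 8 drop-outs per arm, so 22 evaluable per arm. The two-sided test comes from the Statistical analysis section. No SD is given, so the figure cannot be reproduced from the document alone. With an assumed SD of 1.0:

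- n per arm = 2 × (1.960 + 1.282)² × 1.0² / 1² = 21.02, rounded up to 22
- 22 / (1 − 8/30) = 30 randomised per arm

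This matches. Solving back from 22 evaluable per arm gives an SD of 1.02 (normal approximation) or 1.00 (noncentral t). For comparison, an SD of 0.9 would need 25 per arm and an SD of 1.1 would need 36. The calculation uses one outcome, one time and the full 0.05, so the stated level and power belong to JAFI-IMP at six months and to no other comparison.

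**2. The comparisons each section makes primary.**

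| Section | Dimensions | Times | Comparisons |
|---|---|---|---|
| Sample size | impairment | 6 months | 1 |
| Statistical analysis | all three | 6 months | 3 |
| Abstract | impairment | 6 and 12 months | 2 |

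**3. Chance of at least one false positive, in either direction, if each test is at two-sided 0.05.** The level is carried over from the Sample size section; the Statistical analysis section states none.

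Independent tests, 1 − 0.95^k:

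- Three dimensions at six months: 1 − 0.95³ = 1 − 0.8574 = 14.3%
- Impairment at two times: 1 − 0.95² = 1 − 0.9025 = 9.8%

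The dimensions, and repeated scores on one dimension, are likely to be positively correlated. The article gives no correlations, so a range is assumed and normal test statistics with equal correlation were simulated:

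| Assumed correlation | Three dimensions, one time | Impairment, two times |
|---|---|---|
| 0 | 14.3% | 9.8% |
| 0.3 | 13.6% | 9.5% |
| 0.5 | 12.6% | 9.1% |
| 0.7 | 10.9% | 8.3% |
| 0.8 | 9.8% | 7.8% |

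Throughout this range, both the three-test and the two-test reading exceed 5%. With one dimension at one time the rate is 5%, as stated.

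**The case against.** The strongest reply is that the intended primary is not really in doubt. The Sample size section and the abstract both name the impairment domain. Minimisation uses JAFI-IMP. The Sample size and Statistical analysis sections agree on six months, the drop-out allowance covers that same period, and the analysis text speaks of one primary outcome variable. The outcomes section mainly introduces the instrument and need not be read as a rival definition. The abstract's two times may be no more than the measurement schedule. The trial is an exploratory phase II study that sets out to examine the JAFI's suitability for later definitive trials, so looking at every dimension serves a stated purpose.

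Most of this stands, and it lowers the severity. It does not remove the conflict: the sentence that defines the primary analysis says each dimension, and an inferred primary is weaker than a stated one.

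A reader might go further and count six primary tests, three dimensions at two times. The documents do not support that. No section makes that combination primary; even the abstract and the Statistical analysis section taken together give four comparisons (three dimensions at six months, plus impairment at 12). The 12-month scores have their own analysis, which is not labelled primary. A reader might also infer a loss of power at 12 months, but the article gives neither an SD nor any attrition estimate beyond six months, so no such figure can be derived from it.

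**Conclusion.** The point holds as a contradiction in the definition of the primary comparison: three dimensions at six months in the Statistical analysis section, one dimension at six months in the Sample size section, and one dimension at two times in the abstract. Followed literally, the Statistical analysis section carries about a 10–14% chance of at least one false-positive primary result, and the abstract's version about 8–10%. Both ranges assume that each test is done at two-sided 0.05 and that correlations lie between 0 and 0.8.

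It would be too strong to say that the trial has no identifiable primary result, or that three tests at 0.05 without error control are laid down. JAFI-IMP at six months is the natural reading; the 0.05 for the other two dimensions is inferred; and what can be said about error control is only that this article describes none. Given that and the exploratory design, this should be corrected before analysis but is not a must-fix defect.

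**What to change.** In Statistical analysis, name JAFI-IMP at six months as the single primary comparison, tested at two-sided 0.05. It is the only comparison the trial is sized for, so the stated level and power then describe the primary test.

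List activity limitation, participation restriction and all 12-month JAFI results as secondary, reported as estimates with confidence intervals. Bring the abstract (which time is primary) and Initial assessments and outcome measures (which dimension is primary) into line.

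The change is to wording only; the number of patients, the visits and the data collected stay the same. The small downside is that the other two dimensions and the 12-month results can no longer support a primary claim.

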#### Patient follow up procedures

All participants regardless of allocation will undergo another full assessment once they have proceeded to the end of the trial (12 months from baseline). In the interim period, the primary outcome questionnaire (JAFI) will be posted at 6 months from baseline with a stamped-addressed envelope in order to complete and return to the study personnel. Non-responders will be sent a second questionnaire within 2 weeks, followed by a third a further two weeks later, and then contacted by written letter/telephone. Participants in the intervention arm will receive return appointments every 3 months. Any additional appointments within the intervention arm will be made within the scope of normal clinical practice.

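### The named primary test can use only patients with a six-month JAFI score, although 8 of 30 per arm are expected to drop out by then; it is biased if that loss relates to outcome differently in the two arms.

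*Protocol article*

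**What the plan says.** The Statistical analysis section of the protocol article fixes the primary comparison: "The primary analysis will compare the JAFI scores for each dimension between the intervention and control group at six months from baseline". On method it says: "This is to be conducted using a two-sided t-test". A Mann-Whitney test may replace the t-test if change scores are skewed. A repeated measures ANOVA of the 0, 6 and 12 month scores is listed separately and is not the primary analysis.

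The Sample size section is written for the impairment domain (JAFI-IMP): "Sixty patients (30 in each trial arm) will allow detection of a 1 point reduction in the JAFI-IMP score", "at a significance level of p < 0.05 and power of 90"%. It allows for an "estimated potential participant drop out rate over the first six months of the trial (8 patients in each trial arm").

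The abstract states: "Intention to treat data analysis will be conducted". The article does not define this further.

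On collection, the follow-up section says that "the primary outcome questionnaire (JAFI) will be posted at 6 months from baseline". Non-responders get two repeat mailings and are then contacted by letter or telephone. The same section gives 3-monthly return visits for the intervention arm and a full assessment at 12 months for everyone. The Blinding section says that patients will know their arm.

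**The concern.** A two-sample test has no term for baseline, covariates or a later measurement. A patient without a six-month score contributes nothing to it unless a value is filled in, and the article names no way of doing that. The plan expects this to affect about a quarter of each arm.

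The design gives reasons why the loss might not be random. Patients know their allocation. Before the primary questionnaire, the intervention arm has scheduled contact that is not stated for the control arm. The outcome itself arrives by post. A control patient who is doing badly and an intervention patient who is doing badly may therefore differ in how likely they are to supply a score. If so, the test estimates a difference between two differently selected groups, and the result would be reported as the randomised effect.

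The trial will also hold useful data that the test leaves aside. Baseline JAFI-IMP is recorded before allocation and is a minimisation factor. A 12-month JAFI may exist for some patients who lack the six-month one.

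**Working it through.** **Inputs.** From the Sample size section: 30 per arm, 8 lost per arm by six months, a difference of 1 point, two-sided 5% level (the two-sided test is from Statistical analysis) and 90% power. The SD is not stated, so SD = 1.0 is an assumption; a range is shown below.

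**Reproducing the plan's figure.**
- Loss: 8/30 = 26.7%, which leaves 30 − 8 = 22 per arm.
- With SD 1.0, the sample size formula for two means gives 22 per arm, and 22/(1 − 8/30) = 30.
- Exact t-test power with 22 per arm is 0.900. With all 30 observed it would be 0.97.
- Other SDs before dropout: 0.8 gives 14, 0.9 gives 18, 1.1 gives 26 and 1.2 gives 31 per arm.

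The stated size thus fits a test on 22 observed scores per arm with an SD of about 1.0.

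**Bias from loss in one arm.** Let g be the mean of the missing patients minus the mean of the observed patients in one arm, with random loss in the other. The full-arm mean is (22/30) × observed mean + (8/30) × missing mean. The observed mean is therefore off by (8/30) × g in size.
- g = 0.5: 0.267 × 0.5 = 0.13 points
- g = 1.0: 0.267 × 1.0 = 0.27 points

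**Effect on the 5% test.** SE = SD × √(2/22) = 0.30 at SD 1.0. The noncentral t distribution has 42 degrees of freedom and noncentrality bias/SE.
- g = 0.5: 0.133/0.302 = 0.44, error 7%
- g = 1.0: 0.267/0.302 = 0.88, error 14%

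For the same two gaps, SD 0.8 (SE 0.24) gives 8% and 19%, and SD 1.2 (SE 0.36) gives 6.5% and 11%.

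**When the bias arises.** Simulation with no true effect, SD 1, 30 per arm and a t-test on observed scores:

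| Missing (intervention/control) | Mechanism | Bias | Error |
|---|---|---|---|
| 8/8 | random in both | 0 | 5% |
| 4/12 | random in both | 0 | 5% |
| 8/8 | worse scores lost in both | 0 | 7% |
| 8/8 | worse scores lost in intervention, random in control | −0.31 | 20% |
| 12/4 | worse scores lost in both | −0.28 | 19% |

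Unequal rates alone do no harm, and equal numbers lost give no protection. What matters is loss that relates to outcome and acts differently in the two arms.

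**What an alternative would gain.** In further simulations with no true effect, control loss depended on baseline and/or 12-month state and intervention loss was random. Correlations were 0.5 to 0.7, with 8 of 30 missing per arm.
- Unadjusted t-test: bias about 0.13 to 0.32 across variants, SE about 0.30.
- Adjusting for baseline alone: bias 0.00 to 0.10, SE 0.22 to 0.28.
- Adding 12-month scores that are complete: bias about zero.
- Imputing when the 12-month score is also missing for the lost patients: bias 0.05 to 0.07 wherever loss depended on 12-month state.

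**The case against.** The strongest reply is that the article does not say the t-test is limited to patients with scores. It is silent on missing data, and a condensed article may leave that to the full protocol or analysis plan. That is right, and the silence is not the point here. What remains is that the primary test is named, and as named it cannot use an incomplete patient.

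A reader might infer that the plan contradicts its own promise of intention to treat. The text does not support that. An allowance for dropout is a power calculation, not an analysis-set rule, and patients can be analysed in their allocated arm while some are missing.

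A reader might also take the 8 per arm as the expected number of unreturned forms. The text speaks of dropout, and the follow-up section plans repeat mailings and then personal contact. Either way the six-month score is missing. The distinction does weaken the remedy, because patients who have left the trial may have no 12-month score either.

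Three further points stand in part. Control patients are not without contact, since usual medical care and podiatry continue. The mention of change scores suggests that the tested variable may already draw on baseline; even so, a patient without a six-month score has no change score. The trial is exploratory, which lowers the stakes but does not remove the bias from its main result.

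**Conclusion.** The concern holds in a limited form. The named primary test rests on patients with a six-month score, planned at 22 of 30 per arm. It is biased if the loss relates to outcome differently in the two arms. The design makes that plausible; nothing in the article shows that it will happen.

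At an assumed SD of 1.0, a gap of 0.5 to 1.0 points in one arm, with random loss in the other, gives a bias of 0.13 to 0.27 points and a type I error of 7% to 14%. For comparison, the effect the trial is sized to detect is 1 point. These are illustrations, not predictions. A gap of 1.5 points would give 0.40 points and 25%, but nothing in the article supports so large a difference confined to one arm.

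It would also be too strong to say that imputation removes the problem. Most of the gain comes from baseline adjustment. Near-zero bias needs 12-month scores for the patients who were lost, and loss that is random given the data used.

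**What to change.** Reword the primary analysis as follows:
- Compare six-month JAFI-IMP between arms as allocated. Use a likelihood-based model of the 6- and 12-month scores, adjusted for baseline JAFI-IMP, age and gender (the minimisation factors), with the six-month contrast as primary. Multiple imputation with the same variables is an alternative.
- Add a sensitivity analysis that shifts the missing scores separately in each arm, for example by 0 to 1 point.
- Report six-month completion by arm.
- Keep the t-test or Mann-Whitney test as a supportive analysis, labelled as completers only.

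This changes analysis wording only, with no new data, visits or patients. The price is a slightly more complex primary analysis that relies on a missing-at-random assumption, which the sensitivity analysis probes. The 12-month score helps only for patients who have one.

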### Randomisation

Treatment allocation will be conducted by means of minimisation, a highly effective method of allocation which has been recommended for use in randomised controlled trials [33]. Using this method, treatment allocated to the next trial participant depends on the characteristics of those participants already enrolled, with the ultimate aim of 'minimising' the imbalance between groups [34]. Minimisation in this case will be adopted to achieve balance between groups using the following characteristics:

(i) Age

(ii) Gender

(iii) JAFI-IMP score

This method will be conducted by the same researcher (GH) using the minimisation software package Minim [35].

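### The primary t-test leaves out the minimisation factors and does not settle whether scores or changes are analysed; the result is a conservative, less efficient test, not extra false positives

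*Protocol article*

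**What the plan says.** The Randomisation section allocates by minimisation: "Minimisation in this case will be adopted to achieve balance between groups using the following characteristics", and lists age, gender and the JAFI-IMP score. The last is the baseline value of the primary outcome.

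The Statistical analysis section defines the primary analysis as a comparison of JAFI scores between arms at six months. Of the test it says: "This is to be conducted using a two-sided t-test". No covariate is named. The next sentence gives the alternative: "Should the distribution of change scores be skewed, a Mann Whitney test may be used to analyse the primary outcome variable". It sets no criterion for skew.

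The Sample size section gives the design target: "Sixty patients (30 in each trial arm) will allow detection of a 1 point reduction in the JAFI-IMP score" at six months, "at a significance level of p < 0.05 and power of 90" per cent, allowing for the "estimated potential participant drop out rate over the first six months of the trial (8 patients in each trial arm").

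For gait, changes to 12 months are to be "investigated within each treatment group using a one-sample procedure (t test or Signed Ranks test") and are also compared between arms with the two-sample equivalent.

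**The concern.** Three features of the primary analysis do not fit together.

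- **Allocation and analysis are mismatched.** Minimisation forces the arms to be alike on baseline JAFI-IMP. If baseline predicts the six-month score, the difference in means varies less between possible trials than the t-test assumes. The test does not use the balance that the design has created.
- **The variable is not settled.** Six-month scores and changes from baseline have different variances, so the power of the primary test depends on which is meant.
- **The test is not settled.** A t-test estimates a difference in means; a Mann-Whitney test compares rank ordering. Choosing between them after seeing the data leaves open which quantity the trial reports. The issue is foreseeable: each JAFI dimension is scored as a median of 0-4 items, and a median of nine such items is an integer from 0 to 4.

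At stake are the width of the primary confidence interval and some power in a trial expecting 44 evaluable patients. The gait plan has a lesser form of the problem: within-arm changes over 12 months in growing children can be significant without any treatment effect.

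**Working it through.** **Inputs from the protocol.** 30 randomised per arm, 8 lost per arm by six months, so 22 evaluable; difference of 1 point; alpha 0.05; power 90%; two-sided t-test; minimisation on three factors.

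**Assumed, because not stated.** SD of JAFI-IMP = 1.0; correlation r between baseline and six-month score from 0 to 0.7.

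**Reproducing the sample size.** n per arm = 2 × (1.960 + 1.282)² × SD² / 1² = 21.0 at SD 1.0, rounded up to 22. Then 22 / (1 − 8/30) = 30 per arm, 60 in total. Power at 22 per arm is 91.3% by normal approximation and 90.0% by the t distribution. The SD implied by 22 per arm and 90% power is 1.02 (normal) or 1.00 (t). An SD of 1.0 therefore fits the stated figures, but it is back-solved and not a protocol value.

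**Power by formula.** The working SD is 1 for six-month scores, √(2(1 − r)) for change and √(1 − r²) for ANCOVA. Power = Φ(1 / (SD × √(2/22)) − 1.960), where √(2/22) = 0.3015.

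| r | Scores: SD, power | Change: SD, power | ANCOVA: SD, power | ANCOVA n per arm for 90% |
|---|---|---|---|---|
| 0.3 | 1.000, 91.3% | 1.183, 80.0% | 0.954, 93.5% | 20 |
| 0.5 | 1.000, 91.3% | 1.000, 91.3% | 0.866, 96.9% | 16 |
| 0.7 | 1.000, 91.3% | 0.775, 99.0% | 0.714, 99.6% | 11 |

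The unadjusted test on scores needs 22 per arm throughout.

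**Why the standard error is too large.** With perfect balance on baseline, the true standard error of the difference is √(1 − r²) times what the t-test reports. The t-test overstates it by up to 1/0.954 = 1.05, 1/0.866 = 1.15 and 1/0.714 = 1.40 at r = 0.3, 0.5 and 0.7. Banding the baseline score and losing patients weaken the balance, so the real excess is smaller.

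**Simulation.** 3,000 trials per setting; 60 patients minimised deterministically on three age groups, sex and three baseline bands; 44 analysed; SD 1.0; drop-out at random.

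| r | Type I error: t on scores | t on change | ANCOVA | Reported / true SE, t on scores | Power: t on scores | Change | ANCOVA |
|---|---|---|---|---|---|---|---|
| 0.3 | 4.3% | 3.1% | 4.7% | 1.01 | 90.0% | 80.3% | 91.0% |
| 0.5 | 3.2% | 3.0% | 5.0% | 1.07 | 90.7% | 90.9% | 95.3% |
| 0.7 | 2.2% | 3.8% | 4.0% | 1.17 | 93.2% | 99.0% | 99.2% |

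- Under simple randomisation at r = 0.5 the t-test on scores returns to 5.0%, so the cause is the ignored minimisation.
- With two or three baseline bands and a preferred-arm probability of 0.7 to 1, type I error of the t-test on scores is 4.0-4.8%, 3.3-4.2% and 1.9-3.1% at the three correlations. A further run gave 4.0%, 3.8% and 2.1%, against 4.6-5.3% for ANCOVA; power was 90%, 90% and 93% against 92%, 95% and 99%.
- Switching from t-test to Mann-Whitney on a skewness test gave 2.1-5.1%: no inflation.
- ANCOVA on integer scores from 0 to 4 held 4.5-4.8%.

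**The case against.** The best defence is that the planned test is valid and does what the design promised. On the assumed SD, the unadjusted t-test on six-month scores reaches the stated 90% power, its error rate is at or below 5%, and the trial is exploratory. Skewness thresholds are commonly left to an analysis plan. All of that stands. It means that lost power is relative to an adjusted analysis, and that a missing threshold is not in itself a fault. It does not answer the mismatch, because the protocol names the primary test and names both scores and changes; these are stated rules and not omitted detail.

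Three stronger readings are tempting and not supported.

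- *Type I error is inflated.* A reader might infer this from an error rate that is not 5%, or from the choice between two tests. The departure is downward, and the protocol ties the switch to skew, not to the smaller p-value.
- *Baseline is ignored altogether.* If changes are analysed, baseline is used, though inefficiently at low correlation, and the standard error is still too large.
- *Gait conclusions rest on within-arm tests.* The protocol also specifies the between-arm comparison, and compares the core spatiotemporal parameters with age and gender norms.

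The figure of about 80% power for change scores at r = 0.3 also requires the SD of 1.0 to be cross-sectional. If it were the SD of change, the change analysis would have 90% power at any correlation. The protocol does not say which.

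**Conclusion.** The point holds as one of efficiency and pre-specification. The primary test omits the factors used to balance the arms, the analysed variable is contradictory, and the choice of test is discretionary. The t-test on six-month scores is conservative: type I error is about 4%, 3-4% and 2% at correlations of 0.3, 0.5 and 0.7. Adjustment raises power by about 2, 5 and 6 percentage points (90% to 92%, 90% to 95%, 93% to 99%), which is slight at 0.3 and material from 0.5.

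These sizes rest on an assumed SD of 1.0, an assumed range of correlation, drop-out at random, no age or sex effect on outcome, and assumed minimisation categories. The protocol gives neither the categories nor any random element. Age or sex effects would increase both the standard error excess and the gain from adjustment. The planned test is usable but suboptimal; the change should be made, but the trial is not invalid without it.

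**What to change.** Make the primary analysis an ANCOVA of six-month JAFI-IMP on arm, adjusted for baseline JAFI-IMP, age group and gender, and report the adjusted mean difference with its 95% confidence interval. This settles the analysed variable. Replace the skew-triggered switch with one named rank-based or ordinal analysis as a sensitivity analysis, reported whatever the distribution looks like.

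For gait, rest any treatment conclusion on the between-arm comparison at 12 months, adjusted for baseline, and present the within-arm tests as descriptive only.

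The cost is analysis wording. The protocol already records age, gender and baseline outcome measures before allocation, so no new data, visits or patients are needed.
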